### Objectives and hypotheses

To date, no studies have assessed whether the health impact of following dietary guidelines is dependent on food processing, nor whether providing behavioural support to UK adults living with overweight/obesity can help to reduce their UPF intake.

Therefore, this study aims to compare the health effects between MPF and UPF diets that follow the EWG recommendations, and the feasibility and acceptability of a behavioural support programme to reduce UPF intake and be more physically active.

The primary objective is to compare weight change between MPF and UPF diets following EWG recommendations (table 1). Secondary objectives are to compare changes in cardiometabolic, behavioural, mental and hormonal outcomes between MPF and UPF diets following EWG recommendations and explore the feasibility and acceptability of the behavioural support intervention.

**Table 1 T1:** UPDATE trial design based on PICOT

Population	Adults (UCLH staff) living with overweight or obesity, and with ≥50% of habitual energy intake from UPFs
Intervention	A minimally processed diet complying with UK EWG guidance
Comparator	An ultra-processed diet complying with UK EWG guidance
Outcome (primary)	Mean difference in percent weight change between intervention and comparator at 8 weeks
Timepoints	Primary outcome assessed from baseline to 8 weeks follow-up on each diet

EWG, Eatwell Guide; UCLH, University College London Hospitals; UPDATE, Investigating the effects of Ultra-Processed versus minimally processed Diets following UK dietAry guidance on healTh outcomEs; UPF, ultra-processed food.

We hypothesise that there will be a difference in the change in weight and other health measures between the two diets; whereby consuming an ad libitum MPF diet complying with the EWG will result in weight loss and favourable changes in cardiometabolic, behavioural, mental and hormonal outcomes, whereas consuming an ad libitum UPF diet complying with the EWG will result in no change in weight or cardiometabolic, behavioural, mental and hormonal outcomes. If the hypotheses are supported, the results would indicate important health implications of the foods that make up the majority of the energy intake of the UK adult population and the differential impact of UPF and MPF, regardless of following current NHS dietary guidance. The results have the potential to substantially impact on dietary guidelines and the dietary management of obesity worldwide, supporting the development of regulations around the marketing and labelling of UPFs, and increasing knowledge and public awareness of the health consequences of UPFs.^28^ The results are directly relevant for UK public health food policy as the interventions are based on the UK EWG. Given the similarities between UK and other national dietary guidelines, there will be important implications for guidelines worldwide as well.

## Methods and analysis

### Trial design and study setting

UPDATE (Investigating the effects of Ultra-Processed versus minimally processed Diets following UK dietAry guidance on healTh outcomEs) is a single-site, community-based, 2×2 cross-over randomised controlled trial (RCT) followed by a 6-month behavioural intervention, conducted in the UK by the Centre for Obesity Research, Division of Medicine, University College London (UCL) and UCL Hospitals (UCLH). The protocol was designed according to Standard Protocol Items: Recommendations for Interventional Trials guidelines (https://www.spirit-statement.org).^29^

In summary, 55 adults aged 18 or older, living with overweight/obesity (between 25 kg/m^2^ and 40 kg/m^2^), with 50% or more of habitual energy intake from UPFs will be recruited. Participants will receive an 8-week, minimum 80% UPF diet and an 8-week, minimum 80% MPF diet, both following UK EWG macronutrient recommendations, in a random order, with a 4-week washout period. All food and drink will be provided. All participants will then receive a 6-month behavioural support programme to reduce UPF (figure 1).

**Figure 1 F1:**
[figure not shown]
Flow chart of UPDATE trial. AE, adverse events; BIA, bioimpedance analysis; BP, blood pressure; HR, heart rate; RCT, randomised controlled trial; UCLH, University College London Hospitals; UPDATE, Investigating the effects of Ultra-Processed versus minimally processed diets following UK dietary guidance on health outcomes; UPF, ultra-processed food; WC, waist circumference.

The trial is funded by the National Institute for Health (NIH) and Care Research UCLH Biomedical Research Council (MRC) and Rosetrees Trust, and UCL/UCLH are the sponsors. The sponsor and funders were not involved in the design and conduct of the trial.

## Methods: participants, interventions and outcomes

The trial opened to recruitment on 13 January 2023, the first individual was screened on 13 March 2023, and the first randomisation on 4 April 2023. The planned end date is 31 March 2025.

### Recruitment

Potential participants will be identified through advertising at UCLH/UCL (eg, websites, Trust email, posters, internal communications) and on social media (Twitter).

Interested individuals will receive a participant information sheet (PIS) (online supplemental material 1) and be offered a phone call with the research team. Researchers will then explain the screening procedure and the aims, methods, anticipated benefits and potential hazards of the trial, and invite individuals to attend an in-person visit to undergo screening. Written informed consent will be sought a minimum of 24 hours after receiving the PIS, at the in-person visit (see online supplemental material 2 for the approved consent form). Participants can withdraw at any time, without giving a reason.

10.1136/bmjopen-2023-079027.supp1Supplementary data

10.1136/bmjopen-2023-079027.supp2Supplementary data

### Eligibility criteria

Written informed consent will be obtained prior to commencing screening based on the inclusion and exclusion criteria, and before any research-associated measurement is taken (table 2).

**Table 2 T2:** Eligibility criteria

Inclusion criteria	Exclusion criteria
Staff at UCLH	Contraindication for dietary intervention
Adults aged ≥18 years	Participation in another clinical intervention trial
BMI ≥25 kg/m^2^ (living with overweight or obesity)	Concomitant recent usage of medications that cause weight gain or weight loss
Weight stable (≤5% variation in body weight over preceding 3 months)	Cardiometabolic comorbidities (eg, diabetes, on insulin)
Have a habitual dietary intake consisting of ≥50% UPF intake as % total daily energy intake	Coeliac disease
Able to read and write in English	Inflammatory bowel disease
Medically safe to participate in a dietary intervention programme	A diagnosed eating disorder
Willing and able to give written informed consent	Planning a weight management programme in the next 3 months
Able to attend the relevant in person and remote sessions	Any diagnosed food allergy, or other allergies which limit the ability to adhere to the intervention diet
Able to comply with the study protocol (including dietary recommendations for each intervention and reporting adherence)	Dietary restrictions (eg, vegan, vegetarian, halal or kosher) which limit the ability to adhere to the interventions
Females of childbearing potential and males agree to use an effective method of contraception from the time consent is signed until the end of the intervention period and final follow-up assessment. Effective methods of contraception acceptable for UPDATE are outlined in the online supplemental material 3	BMI >40 kg/m^2^ or basal metabolic rate ≥2300/kcal/day (to ensure intervention diets are at least 300kcal/day greater than maintenance energy needs, based on excess energy intakes reported in Hall *et al* 21
Females of childbearing potential must be on highly effective contraception and have a negative pregnancy test	Females who are pregnant, breast feeding or intend to become pregnant
	A history of drug or alcohol abuse
	Any other factor making the participant unsuitable in the view of investigator

BMI, body mass index; UCLH, University College London Hospitals; UPDATE, Investigating the effects of Ultra-Processed versus minimally processed Diets following UK dietAry guidance on healTh outcomEs; UPF, ultra-processed food.

10.1136/bmjopen-2023-079027.supp3Supplementary data

Participants will complete two non-consecutive 24-hour recalls at screening. If they meet all inclusion criteria and do not meet any exclusion criteria, they will complete a further two non-consecutive 24-hour recalls at baseline to confirm a habitual dietary intake of ≥50% UPF. The mean of all four recalls will be used to determine final habitual UPF intake. After which, they will be considered eligible.

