### Outcomes

Outcome measures will be collected at seven in-person visits. See figure 1 and online supplemental material 5 for the schedule of assessments.

10.1136/bmjopen-2023-079027.supp5Supplementary data

The primary outcome is the mean difference in percent weight change (%WC) at 8 weeks from baseline between MPF and UPF diets. This outcome is currently being used clinically in weight management clinics and used for all NHS weight management programmes. Clinically significant weight change can occur from short-term dietary interventions and directly relates to improvements in cardiometabolic risk factors (eg, blood pressure, blood glucose, glycated haemoglobin (HbA1c), lipids),^42^ physical function and quality of life.^43^ Weight is an efficient and more accurate measurement to collect than other energy balance measures, such as energy intake. The hypothesised %WC in the face of the current growing obesity pandemic would have clinically relevant impacts on halting the rate of progression of obesity prevalence and mitigating the adverse impacts of adiposity-related disease, simply through shifts in the types of processed in foods being consumed.

Secondary outcomes include changes in dietary intake, waist circumference, body composition (fat mass, fat-free mass), heart rate, blood pressure, cardiometabolic risk factors (comorbidities and blood biomarkers including liver function, lipid profile, glucose, HbA1c and C reactive protein), fasted and fed metabolomics, appetite measures (fasted and fed appetite scores, circulating gut hormones and adipocytokines), sleep, sleep quality, PA levels, physical function (walking distance, leg strength, handgrip strength), mental health, quality of life, well-being and aspects of eating behaviour between MPF and UPF diets, and after the 6-month behavioural intervention compared with the first baseline assessment. In a subset of participants, changes in brain functional resting state connectivity between MPF and UPF diets will be assessed. Further behavioural intervention secondary outcomes include understanding the experiences of UPF versus MPF diets, changes in behaviour regulation and shopping expenditure from the first baseline assessment, and barriers and facilitators to reducing UPF intake.

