#### Assessment of dietary adherence and intake

In line with previous trials,^71^ multiple approaches will be used to assess dietary intake and adherence, including 24-hour recalls, food frequency questionnaires (FFQ) and image-based dietary assessment (IBDA).

Intake24^72^ is a validated, online, self-reported 24-hour recall system, based on a multiple-pass recall suitable for the general population^73 74^ (https://intake24.co.uk). The web-based recall method is convenient, efficient and ensures coding consistency. Participants enter all food and drink consumed in the previous 24 hours (from waking up to going to sleep) into Intake24 on two non-consecutive days per visit period. Each recall takes roughly 12 min to complete.^75^ The first recall at screening will be conducted with the research team to ensure adequate training. Links will then be sent to participants to complete further recalls remotely. Intake24 is connected to the National Diet and Nutrition Survey Nutrient Databank to provide nutrient outputs and has been coded into NOVA by the research team for calculating UPF/MPF intake.^76^ Intake24 includes details on the brand names of products, facilitating assignment of NOVA groups.

The European Prospective Investigation into Cancer and Nutrition (EPIC)-Norfolk FFQ is a validated, semiquantitative measure of average dietary intake over the past year.^77–79^ The FFQ contains a 130-item food list followed by detailed questions regarding the food list. For each food item, participants tick the most appropriate frequency of consumption of that item from nine options (from never or less than once per month, to 6+ per day).

Participants will complete an FFQ and two non-consecutive day 24-hour dietary recalls at baseline, and 4 weeks and 8 weeks for both diets and at the 6-month behavioural intervention follow-up (figure 1).^80^ IBDA will also be completed on two non-consecutive days during weeks 4 and 8 of the RCT, whereby participants will take photos before and after their ad libitum meals/snacks.

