## Ethics and dissemination

### Research ethics approval

The Yorkshire & The Humber—Sheffield Research Ethics Committee approved the trial on 22 December 2022 (22/YH/0281), and the study was prospectively registered on ClinicalTrials.gov (NCT05627570). The trial is currently recruiting and ongoing. The trial will be conducted in compliance with the principles of the Declaration of Helsinki 1996 and the principles of the International Conference on Harmonisation GCP. Any amendments will be recorded in academic publications and will be submitted for approval to the Sponsor and Research Ethics Committee prior to implementation. Protocol V.1.3, 26 July 2023. Sponsor contact: (UCLH/UCL) Joint Research Office ([contact]). On 16 June 2023, the UPF intake inclusion criterion was amended from ≥60% to ≥50% to better reflect the average intake of participants in London, compared with intakes across the UK.^9^

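### The first-baseline recalls help decide entry at ≥50% UPF and are also the comparator for the 6-month change, so regression to the mean is expected to inflate the recorded fall in UPF intake

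*Protocol article*

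**What the plan says.** The inclusion criteria in Table 2 require that participants "Have a habitual dietary intake consisting of ≥50% UPF intake as % total daily energy intake". The text under Eligibility criteria gives the procedure. First, "Participants will complete two non-consecutive 24-hour recalls at screening". Those who pass then return for more: "they will complete a further two non-consecutive 24-hour recalls at baseline to confirm a habitual dietary intake of ≥50% UPF". Finally, "The mean of all four recalls will be used to determine final habitual UPF intake".

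The section Assessment of dietary adherence and intake has recalls entered "on two non-consecutive days per visit period" and schedules the outcome data: "Participants will complete an FFQ and two non-consecutive day 24-hour dietary recalls at baseline", with repeats at weeks 4 and 8 of each diet and at 6 months. Intake24, the recall tool, is the only diet instrument described as coded to NOVA. The food frequency questionnaire is not.

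The Outcomes section lists dietary intake among the secondary outcomes assessed "after the 6-month behavioural intervention compared with the first baseline assessment". Under Trial design and study setting, every participant receives the behavioural programme.

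Under Research ethics approval, "the UPF intake inclusion criterion was amended from ≥60% to ≥50% to better reflect the average intake of participants in London", with effect from 16 June 2023. The first randomisation was on 4 April 2023.

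**The concern.** With two recalls per visit period, the two that confirm eligibility at baseline are also the baseline dietary data. A one-day recall varies from day to day. People who clear a lower cut-off on a few such days are, on average, recorded above their own habitual level. The 6-month recalls pass through no such filter, so they should sit closer to habitual intake and the difference should be a fall.

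This is separate from the lack of a control group. It is a known-direction error in the baseline value itself, and it favours the hoped-for result. Reducing UPF is the programme's primary target behaviour (Behavioural intervention), and the strengths and limitations box says the protocol covers the programme's effectiveness in reducing UPF intake. A recorded fall could therefore be credited to the programme when part or all of it comes from the entry rule.

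**Working it through.** **Figures in the plan.** There is none for the 6-month change in UPF share or its variance. The Sample size section gives 44 evaluable participants (55 × 0.80 = 44) for weight. I use 44 as an assumed number of completers.

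**Assumptions.** True UPF share is Normal with mean μ and between-person SD s_b. Each recall adds independent error with SD s_w. True intake never changes. S is the mean of the two screening recalls, B the mean of the two baseline recalls, and M = (S + B)/2. Entry requires S ≥ 50 and M ≥ 50, because the article asks for further recalls only from those who already meet the criteria at screening.

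**Middle case by hand: μ = 50, s_b = 10, s_w = 20.**

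1. Var(S) = 100 + 400/2 = 300, SD 17.32. Var(M) = 100 + 400/4 = 200, SD 14.14. Cov(S, M) = 100 + 400/4 = 200. Correlation ρ = 200/√(300 × 200) = 0.816.
2. P(both ≥ 50) = 1/4 + arcsin(0.816)/(2π) = 0.402.
3. Given entry, each standardised variable has mean (1 + ρ)/(2√(2π) × 0.402) = 0.901.
4. Mean S is 50 + 0.901 × 17.32 = 65.6. Mean M is 50 + 0.901 × 14.14 = 62.7. As B = 2M − S, mean B is 50 + 25.49 − 15.61 = 59.9.
5. Mean true intake is 50 + (100/200) × 12.75 = 56.4.
6. Expected spurious fall from the two baseline recalls = 59.88 − 56.37 = **3.5 points**.

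**Chance of a significant fall in that case.** The SD of the change is about 19.0 by simulation (20 without selection, from √(2 × 400/2)). The noncentrality is 3.51/(19.0/√44) = 1.22. With 43 degrees of freedom the two-sided 5% paired t-test declares a fall in about 22% of trials, against 2.5% nominal in that direction.

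**Range by simulation, same entry rule, two-recall baseline:**

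| Source mean | Between-person SD | Day-to-day SD | Expected spurious fall (points) |
|---|---|---|---|
| 55 | 14 | 15 | 1.2 |
| 50 | 10 | 20 | 3.5 |
| 45 | 10 | 25 | 6.4 |
| 55 | 15 | 10 | 0.5 |
| 60 | 10-15 | 10 | 0.4 |
| 60 | 10-15 | 15 | 0.9 to 1.0 |
| 60 | 10-15 | 20 | 1.5 to 1.7 |
| 60 | 10-15 | 25 | 2.3 to 2.6 |

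The first three rows are the ends and middle of the main grid (mean 45-55, between-person SD 10-14, day-to-day SD 15-25). Over that grid the chance of a significant fall runs from 8% to 44%. The other rows show where the effect becomes small.

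**Alternative entry rule.** If only M ≥ 50 selects, the middle case is (400/4)/14.14 × 0.798 = 5.6 points.

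**Comparator outside the selection.** With recalls that played no part in entry, such as those at the second baseline, the expected change under the same constant-intake model is within 0.1 point of zero.

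**The case against.** **The phase is exploratory.** The Behavioural intervention section says the study is not powered for this part and aims at feasibility and acceptability. The feasibility section makes calls delivered and retention the main outcomes and defers the full evaluation to a later paper. This stands, and it limits the weight of the point. It does not remove it: the article itself fixes both the entry rule and the comparator, and it also speaks of effectiveness.

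**First baseline is a defensible comparator.** It is the only assessment before any study diet. This also stands, and it is why that comparison should be kept.

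**A correction is analysis-plan detail.** Agreed. The absence of a regression-to-the-mean correction from the article is not itself a fault.

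Stronger readings that the documents do not support:

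- A reader might infer that a fall will certainly be seen. The result holds in expectation only. In the middle case a significant fall appears in about one trial in five.
- A reader might take the four-recall mean as the outcome baseline, which would give 2.5 to 10.8 points on the main grid (62.7 − 56.4, or 6.4 before rounding, in the middle case). The article uses that mean for eligibility. The outcome schedule has two recalls per visit period, so the two-recall figures are the natural reading.
- A reader might suppose that randomised diet order makes the second baseline an unbiased reference. It balances a contrast between orders, but leaves any shift common to both.
- A reader might suppose that the four entry recalls of those admitted suffice for a correction. They do not, because the source mean and between-person variance are also needed.

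**Conclusion.** The point holds for one comparison: the uncontrolled 6-month change in UPF share from first baseline. Its direction follows from the entry rule and the choice of comparator. Its size cannot be fixed from the article, because every variance used here is assumed. The expected spurious fall is about 1.2 to 6.4 points on the main grid and 3.5 in the middle case. It can be below 1 point if day-to-day variation is low, or if volunteers average about 60% and that variation is moderate.

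The stated reason for lowering the cut-off suggests that local intake lies near or below the old threshold, which does not favour the mildest cases. Anyone admitted under the ≥60% rule was selected further into the upper tail; that is not modelled here and would add to the bias.

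A reader might extend the concern to the trial's main result. The documents do not support that: the randomised comparison of the two diets, the weight outcome and the sample size do not depend on this baseline contrast.

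**What to change.** 1. Keep the comparison with first baseline, and also report the 6-month change in UPF share against the second-baseline recalls (visit 5, after washout) as a sensitivity comparator. Table 4 already schedules Intake24 there, and those recalls play no part in selection. The downside should be stated: a shift common to both diet orders, for example from Eatwell Guide education or from taking part, remains and may understate the change from habitual diet.
2. If a regression-to-the-mean correction is added, base it on the recalls of everyone screened, including those screened out, where these are retained. It needs the source mean and the between-person variance as well as the within-person variance.
3. State that the uncorrected fall from first baseline is not by itself evidence that the programme reduced UPF intake, and bring the effectiveness wording in the strengths and limitations box into line with the feasibility aim.

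The cost is analysis and reporting text. Items 1 and 3 need no new visit, recall or change to recruitment. Item 2 depends on whether the recalls of people screened out have been kept, which the article does not say.

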### Interventions

Eligible participants will receive in a random order (1) an 8-week MPF diet (at least 80% MPF (NOVA group 1), <20% UPF) and (2) an 8-week UPF diet (at least 80% UPF, <20% MPF), both following EWG recommendations. During the 4-week washout between diets, participants will return to their habitual diet to minimise carryover effects.

Participants will be given all meals, snacks and drinks for each 8-week intervention to maximise adherence, ensure internal validity and minimise dropout.^30 31^ Catering companies and supermarkets will deliver diets to participants’ homes, two times per week. Deliveries will be scheduled according to participants’ convenience.

Both diets will follow EWG recommendations, choosing foods with green or amber front of package traffic lights for total fat, saturated fat, sugar and salt over foods with red traffic lights, consuming five portions per day of fruit and vegetables, and eating a variety of foods in the right proportions.^18^

Diets will be matched for and aim to follow government recommended intakes for a 2000kcal/day diet^4 18^ (table 3). Provided diets will be scaled up to 4000 kcal/day, to ensure participants are not energy restricted and energy intake is ad libitum.

**Table 3 T3:** Eatwell Guide dietary recommendations^4 18^

Component	Guidance
Total fat	35% of provided energy intake or below, 78 g or less/2000 kcal
Saturated fat	10% of provided energy intake or below, 24 g or less/2000 kcal
Salt	Less than 6 g per day. Intake in line with current UK average intakes,^94^ aiming for below 6 g per day
Carbohydrate	Around 50% of provided energy intake, 267 g/2000 kcal
Total sugars	Less than 90 g/2000 kcal, less than 18% of total energy
Protein	Around 15% of provided energy intake, 45 g/2000 kcal
Fibre	At least 18 g/2000 kcal
Fruit and vegetables	Five portions per day

The menus will be designed to be representative of UK diets, by identifying the most commonly consumed foods in the UK National Diet and Nutrition Survey.^32^ Practical and logistical aspects including price, best-before dates, storage requirements and accessibility will be factored into the design. Diets will be matched where possible, with MPF/UPF versions of the same meals (eg, Caesar salad, salmon and potatoes, porridge/breakfast cereal). UPF items are typically foods obtained from supermarkets, whereas MPFs are freshly made culinary preparations. The menu will vary across the week to prevent participant boredom and sensory-specific satiety,^33^ but repeating each week to allow consistency and reduce burden. Alcohol will not be provided. Participants will be asked to keep alcohol consumption within government guidelines (≤14 units per week).^34^ Participants will be educated on the EWG, but further lifestyle guidance will not be given. Menu guides will be provided with instructions and pictures to prepare each meal. As in previous ad libitum feeding trials investigating weight change,^35^ participants will be asked to consume as much or as little of the provided diets as they desire, but they will not be asked to actively reduce their energy intake.

Participants will receive weekly calls from the research team, including dietitians, to discuss any issues with the diets and to promote adherence. Participants will have a food diary to track adherence and to record any food consumed off diet. The 4-week and 8-week diet assessments will also be used for monitoring adherence. Participants will be encouraged to report any deviations from the provided diets during weekly calls and in the food diary and to be as honest as possible, with no repercussions. Previous studies indicate high adherence when all food is provided and delivered to participant homes, where eating foods provided is more of a challenge than eating foods off the diet.^30^ Minor modifications to the intervention that do not alter the overall design will be acceptable for enabling adherence. For example, adding herbs or spices (without sugar/salt) to taste or providing alternative items to facilitate food preparation if participants do not have access to a microwave (eg, swapping a microwaveable meal for a ready-to-eat meal).

